
### Adherence measures

A number of adherence measures will be collected.i)Number of physiotherapist consultations attended for each participant (possible range 0–6);ii)Self-reported number of home exercise sessions in the last two weeks (options of 0, 1, 2, 3, 4, 5 and 6+) at 6 months and converted to a percentage out of the 6 prescribed sessions.iii)Self-rated adherence to the home strengthening program scored on an 11-point NRS in response to the question “I have been doing my exercise sessions the number of times I was asked to by my POWER physiotherapist (e.g. three times per week)” over the previous 6 months where 0 = strongly disagree and 10 = strongly agree;iv)Self-rated adherence with the physical activity plan scored on an 11-point NRS in response to the question “I followed the physical activity plan that my POWER trial physiotherapist helped me to develop” over the previous 6 months where 0 = strongly disagree and 10 = strongly agree;v)Self-rated adherence to the diet program (diet plus exercise group only) scored on an 11-point NRS in response to the question “I followed the diet plan as it was outlined by my POWER trial physiotherapist” over the previous 6 months where 0 = strongly disagree and 10 = strongly agree.

### Intervention fidelity

Physiotherapists will complete bespoke semi-structured electronic treatment notes for each consultation and submit these for review by research staff to ensure adherence to trial intervention protocols. Fidelity will be reported as: i) duration in minutes of each consultation recorded by the physiotherapist; ii) number and proportion of consultations where the physiotherapist has undertaken specific required elements of the intervention protocol (such as set weight loss goal, assessed progress, discussed different educational topics, prescribed exercises, recorded weight).

### Process and other measures

These include:i)Physiotherapists’ contact with trial investigators for advice or support relating to the weight loss program during delivery of the intervention will be recorded by the researchers. Number of physiotherapists who contacted the trial coordinator, number of contacts and reasons for contact will be reported;ii)Participant’s satisfaction with their allocated intervention assessed using a seven-point global rating scale with options ranging from ‘extremely dissatisfied’, to ‘extremely satisfied’. Participants who indicate that they are moderately or extremely satisfied will be categorized as satisfied;iii)Therapeutic alliance assessed using the Working Alliance Inventory Short Form [58]. This will be completed by participants at 6-months while physiotherapists will complete this following the last consultation with the participant. Overall scores for each range from 12 to 84, with higher scores indicating a stronger therapeutic alliance;iv)The attitude of participants towards different clinicians delivering weight loss interventions assessed at baseline and 6 months by response to the statement “I am confident that a [general practitioner / dietician / physiotherapist] could deliver a dietary weight loss program” using a 5-point Likert Scale for each clinician, with terminal indicators of 1 = strongly disagree, to 5 = strongly agree;v)Participants allocated to the diet plus exercise group will be asked to report the total number of weeks they used meal replacements for over the 6 months.vi)Participants allocated to the diet plus exercise group will be asked to respond to 8 custom statements exploring their perception of the knowledge and skills of their physiotherapist and their confidence in, and comfort working with, the physiotherapist for delivery and support of the dietary weight loss program, at the 6 month time point. A 5-point Likert Scale is used for each question, anchored at ‘1’ = strongly disagree, to ‘5’ = strongly agree;vii)Self-efficacy for eating control assessed using the Weight Efficacy Lifestyle (WEL) questionnaire short form. Scored from 8 statements regarding eating control on a 10 point NRS [59] with total scores ranging from 0 to 80 and higher scores indicating greater self-efficacy for eating control;viii)Arthritis self-efficacy scale short form [60] scored from 8 questions on a 10-point NRS with the total presented as an average of the 8 item scores and higher scores indicating higher self-efficacy;ix)Physiotherapists’ confidence in their knowledge and in their clinical skills in weight management assessed using a custom-developed reliable and valid questionnaire [28] (knowledge score range 14–70 and skills score range 9–45, higher indicating greater confidence) before and after undergoing the training and after completion of the trial;x)Physiotherapists self-rated confidence in delivering the ketogenic VLCD on an 11-point NRS anchored at 0 = no confidence to 10 = extremely confident at the end of the study.

### Baseline descriptive measures

Descriptive measures at baseline include: age; height; sex; education level; duration of symptoms; pain at other sites; current employment status; co-morbidities (evaluated using the Self-Administered Comorbidity Questionnaire [61]); dieting history (number of serious weight loss attempts over the last 5 years, reported in categories of 0, 1–2, 3–5, 5–10, more than 10); knee OA treatments used in past 6 months including pain medications; and expectation of treatment outcome (self-reported using a 5-point Likert scale with anchors of “no effect at all” to “complete recovery”).

### Co-interventions

Participants will self-report at 6 months any use of co-interventions (treatments) which they have used to manage their knee pain and reduce their body weight during the trial. Participants will also report at 6 months any pain and arthritis medications/supplements that they have taken at least once per week for their knee problem in the past month.

### Adverse events

Adverse events will be self-reported and are defined as any untoward medical occurrence in a participant that does not necessarily have a causal relationship with the treatment. Participants will be advised to report adverse events to the trial coordinator as soon as possible. Adverse events will also be self-reported in the 6-month questionnaire, where participants are asked to provide details of the nature of adverse event(s), how long they lasted for, what action, if any, they took (e.g. taking medication or seeing a healthcare professional), and whether they believe the adverse event was caused by participation in the trial (likely, unlikely, or unsure).

The chief investigator will determine whether the event is not related, related or possibly related to the participant’s involvement in the trial. Events considered to be related or possibly related will be recorded as related adverse events. Serious adverse events will be defined as any untoward medical occurrence that; i) results in death; ii) is life-threatening; iii) requires hospitalisation or prolongation of existing hospitalisation; iv) results in persistent or significant disability or incapacity; v) is a congenital anomaly or birth defect, or; vi) any other important medical condition which may require medical or surgical intervention to prevent one of the outcomes (i)-(v). We will report the number and proportion of participants who: withdraw from the trial due to a related adverse event; experience one or more serious related adverse events and their types; and experience one or more non-serious related adverse events and their types.

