## Discussion

This protocol describes the background, aims and protocol for a two-group, parallel superiority RCT aiming to compare the addition of a ketogenic VLCD program to exercise delivered by physiotherapists via videoconference versus exercise alone, on weight loss in people with knee OA and overweight or obesity. The effects of the combined program on other clinical outcomes will also be evaluated. A range of process measures will provide insights into the participants’ experience with the diet program delivered by physiotherapists. The findings will help provide evidence as to the effectiveness, safety, feasibility and acceptability of this innovative model of service delivery for weight management that expands the scope of physiotherapists’ practice. Such a service model has the potential to increase patient access to evidence-based weight management programs.

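### Adverse events are collected whatever their cause, but the stated reporting list covers only those judged related or possibly related, so events judged not related would not be shown by arm

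*Protocol article*

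**What the plan says.** All of the rule is in the protocol article, section Adverse events.

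- **Collection.** Adverse events are self-reported and defined as "any untoward medical occurrence in a participant that does not necessarily have a causal relationship with the treatment". Serious events are defined by outcome (death, threat to life, hospitalisation and so on), again without reference to cause.
- **Classification.** "The chief investigator will determine whether the event is not related, related or possibly related" to participation in the trial. The two positive categories are then merged: "Events considered to be related or possibly related will be recorded as related adverse events".
- **Reporting.** The article commits to the number and proportion of participants in three groups: those who "withdraw from the trial due to a related adverse event", and those who "experience one or more serious related adverse events and their types; and experience one or more non-serious related adverse events and their types".

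All three items carry the word related. No count of events regardless of cause is listed there or in the Data analysis plan section. The Discussion says that the findings will help provide "evidence as to the effectiveness, safety, feasibility and acceptability of this innovative model of service delivery".

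**The concern.** Randomisation makes the arms comparable for everything that happens to participants. It does not make them comparable for a subset picked out afterwards by a judgement about cause, because that judgement can itself depend on the arm. Here there is a specific route for this: the diet plus exercise arm receives the whole exercise programme and a ketogenic very low-calorie diet as well, so it has one more candidate cause for any symptom. The same complaint could be classed as possibly related in one arm and not related in the other. The filter could create a difference that does not exist or conceal one that does.

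The second consequence does not depend on any difference in attribution. A participant whose only event is a hospitalisation judged not related meets the protocol's definition of a serious event, yet is counted in none of the three planned summaries. A reader of the trial report could not see how many such participants there were in each arm. With 44 per arm, serious events are likely to be few, and each one left out matters to the description of safety.

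**Working it through.** **1. Collection against reporting.**

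| Event | Recorded? | In the stated reporting list? |
|---|---|---|
| Serious, judged related or possibly related | yes | yes |
| Non-serious, judged related or possibly related | yes | yes |
| Withdrawal due to a related or possibly related event | yes | yes |
| Serious, judged not related | yes | no |
| Non-serious, judged not related | yes | no |
| Withdrawal due to an event judged not related | yes | no |

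The gap follows from the wording of the list and needs no assumption about anyone's behaviour. The article does not state that the summaries are by arm. I read them that way because the trial has two arms and no other use is apparent.

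**2. Denominator.** The protocol gives no figure for adverse event risk, so there is none to reproduce. The only figure borrowed is the arm size in Trial sample size. A difference of 5 with SD 7.5, two-sided 0.05 and power 0.80 gives 36.3 by the t-test, hence 37 per group. Then 37 / 0.85 = 43.5, hence 44 per group. Both stated figures reproduce.

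**3. Possible size of the distortion (assumed inputs).** Let q be the true proportion of participants with an event, equal in both arms. Let a1 (diet plus exercise) and a0 (exercise) be the probabilities that a participant's event is judged related or possibly related.

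- Reported proportion in an arm = q × a
- Spurious difference = q × (a1 − a0)
- Participants with events left out, both arms together = 44 × q × (2 − a1 − a0)

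Example: q = 0.30, a1 = 0.7, a0 = 0.3. Diet plus exercise: 44 × 0.30 × 0.7 = 9.2 participants. Exercise: 44 × 0.30 × 0.3 = 4.0. Difference: 0.30 × 0.4 = 12 percentage points, where the true difference is zero.

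| q | True number per arm | Difference at 0.5 v 0.5 | Difference at 0.7 v 0.3 (reported numbers) | Difference at 0.9 v 0.1 |
|---|---|---|---|---|
| 10% | 4.4 | 0 | 4 points (3.1 v 1.3) | 8 points |
| 30% | 13.2 | 0 | 12 points (9.2 v 4.0) | 24 points |
| 50% | 22.0 | 0 | 20 points (15.4 v 6.6) | 40 points |

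In each of these attribution pairs a1 + a0 = 1, so the number left out is 44 × q, which is half of the 88 × q participants with events. That holds in the 0.5 v 0.5 column too: equal attribution removes the spurious difference but not the omission.

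**4. The opposite direction.** Suppose 3 v 0 participants are hospitalised (3/44 = 6.8% v 0%) and all three events are judged not related. The stated list would show 0 v 0.

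**The case against.** Several points on the other side are fair.

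- **The category is broad.** Possibly related counts as related, and the question is about involvement in the trial, not about the diet alone. Only events judged not related are dropped, and an exercise-arm symptom could also be classed as possibly related. This stands, and it may keep the loss small. It does not bring the remaining events into the report.
- **The events are not lost.** They are recorded whatever their cause, and a Data Safety and Monitoring Committee receives a report every 3 months (Study design), although its content is not stated. This stands: the gap is in the planned report, not in the data or necessarily in the oversight.
- **The list does not say only, and a full statistical analysis plan is promised.** That plan could add an all-cause table. But the article states a definite list, each item restricted in the same way, and nothing in it points to a wider one. This is a rule as written, not a detail left open.
- **No formal comparison is planned.** The article promises numbers and proportions, and no test of adverse events. This stands. In the 3 v 0 example, two-sided Fisher p = 2 × 13244/109736 = 0.24, so an all-cause table would not establish a difference either. Its value is transparency.
- **All-cause counts are not free of bias.** Events are self-reported by participants who know what they receive, so reporting may itself differ by arm. This stands and limits what the fix achieves.

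A reader might also infer that the chief investigator classifies events knowing the allocation. The article does not say so. It is silent, and a condensed article may leave that detail to the full protocol, so the point does not rest on it.

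**Conclusion.** The point holds as a reporting gap. By the stated rule, events judged not related, serious ones included, would be recorded but not shown by arm. The descriptive safety contrast would rest on a causality judgement made after randomisation that could differ between arms.

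The size of any distortion cannot be determined from the protocol. Under assumed equal true risks of 10% to 50% and attribution of 0.7 v 0.3, it is 4 to 20 percentage points; it is zero if attribution is equal and larger if attribution is more unequal. These are illustrations of what the rule permits, not estimates. A reader might take them as evidence that attribution will favour one arm, and nothing in the document supports that. Nor would it be right to conclude that unrelated serious events go unmonitored, since they are collected and may reach the safety committee.

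The primary outcome and the planned tests are unaffected. The change is still worth making, because the article names safety among the things the findings will inform.

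**What to change.** Extend the reporting list in Adverse events, and carry it into the statistical analysis plan, so that it gives by arm the number and proportion of participants with:

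1. any adverse event;
2. any serious adverse event, with types;
3. withdrawal from the trial due to any adverse event;

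each regardless of judged relatedness. Keep the three related-event summaries already planned, labelled as a subset of these.

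The cost is one extra table from data that are already collected, with no new visits, questions or tests. A note to the table should say that events are self-reported by participants aware of their allocation, so the all-cause counts remove the attribution filter but not reporting bias.

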### Trial sample size

Clinical practice guidelines for knee OA recommend patients who have overweight or obesity should lose at least 5–7.5% of body weight [62]. We therefore powered the trial to detect a conservative between-group difference in weight loss of 5% of body weight assuming no change in weight in the exercise group based on previous research [13, 63]. While the between-participant standard deviation of percentage change in body weight was 5% in another study [63], we were more conservative and assumed a larger standard deviation of 7.5% given that our program has substantially less therapist contact (6 in ours compared with up to 12 individual sessions and 42 group sessions in the previous study [63]), which could result in more variation in response. For a power of 0.8 and a two-tailed significance level of 0.05, we required 37 participants per group. We increased this to 44 participants per group (88 in total) to allow for a 15% loss to follow up [34]. Since physiotherapists treat participants in both arms of the trial, we have not adjusted the sample size calculation for clustering by physiotherapist. Due to unknown correlations between percentage weight loss and baseline weight in this population, sample size calculations are conservative and do not account for the adjustment of baseline weight which will further increase the statistical power.

### Data analysis plan

A full statistical analysis plan will be made publicly available while blinded and prior to commencement of formal statistical analysis. A biostatistician (FM, under supervision of [name]) will analyze data blind to group name. Comparative analyses between groups will use intention-to-treat. Multiple imputation will be used to account for missing data if the proportion of missing data for the primary outcome is > 5%.

For the primary outcome, the difference in mean percentage change in body weight will be compared between groups using linear regression modelling adjusting for baseline weight and the stratification variables of sex and physiotherapist. Similar analyses will be conducted for continuous secondary outcomes. We will also calculate the proportion of participants achieving ≥5% and ≥ 10% loss of body weight in both groups. Binary outcomes will be compared between groups using log-binomial regression, adjusting for the stratifying variables of sex and physiotherapist, with results reported as risk ratios and risk differences. Counts and percentages of participants experiencing improvement will be reported in each intervention group. Should the log-binomial regression models fail to converge, logistic regression models adjusting for the stratifying variables will be fitted, with results reported as risk ratios and risk differences. In addition to the intention-to-treat effect, we will obtain the complier average causal effect by making use of the collected adherence data. For all between-group comparisons, 95% confidence intervals and *p*-values will be reported. Standard diagnostic plots will be used to verify model assumptions. It is not anticipated that any interim analyses will be performed in this trial.

### Nested qualitative evaluations

To inform implementation, approximately 15 participants from the diet plus exercise group and all physiotherapists will undergo semi-structured individual interviews to explore their experiences of and attitudes towards physiotherapists delivering a dietary weight loss program. Trial participants will be purposively sampled to provide a spread with regards to sex, age, extent of weight loss and reported satisfaction with the diet program. Questions will explore experiences, acceptability, barriers and facilitators to implementation/uptake and ease of integration into the clinical setting. Interviews will be audio-recorded, transcribed and analysed thematically. The qualitative methodology and findings will have its own ethics application and be reported separately from the main trial protocol and findings.

### Timelines

Ethical approval was obtained from the Human Research Ethics Committee of The University of Melbourne in October 2019. The trial was prospectively registered with Clinicaltrials.gov in Feb 2021. Physiotherapists were recruited and underwent training from March to July 2021. Participant recruitment commenced in October 2021. Covid-19 related restrictions meant that recruitment was delayed. Recruitment is expected to be completed by December 2022. The trial is due for completion by June 2023 when all participants will have completed 6-month data. Analysis of data is due for completion by end of Sept 2023.

### Dissemination

Trial findings will be disseminated through publication in peer-reviewed journals and conference presentations as well as via our Centre website, media and social media including a study infographic. No information which could lead to the identification of a participant will be included in the dissemination of results. Only fully non-identifiable data will be presented when disseminating results.

## Discussion

This protocol describes the background, aims and protocol for a two-group, parallel superiority RCT aiming to compare the addition of a ketogenic VLCD program to exercise delivered by physiotherapists via videoconference versus exercise alone, on weight loss in people with knee OA and overweight or obesity. The effects of the combined program on other clinical outcomes will also be evaluated. A range of process measures will provide insights into the participants’ experience with the diet program delivered by physiotherapists. The findings will help provide evidence as to the effectiveness, safety, feasibility and acceptability of this innovative model of service delivery for weight management that expands the scope of physiotherapists’ practice. Such a service model has the potential to increase patient access to evidence-based weight management programs.

## Data Availability

The deidentified datasets used and/or analysed during the current trial will be made available from the corresponding author on reasonable request.

## Abbreviations

AQoL: Assessment of Quality of Life
BMI: Body mass index
CONSORT: Consolidated Standards of Reporting Trials
CSIRO: The Commonwealth Scientific and Industrial Research Organization
GI: Glycemic index
GP: General practitioner
HREC: Human Research Ethics Committee
iCOAP: Intermittent and Constant Osteoarthritis Pain
NRS: Numeric Rating Scale
OA: Osteoarthritis
PASE: Physical Activity Scale for the Elderly
RACGP: The Royal Australian College of General Practitioners
RCT: Randomized Controlled Trial
SPIRIT: Standard Protocol Items: Recommendations for Interventional Trials
TIDieR: Template for Interventional Description and Replication
VLCD: Very Low Calorie Diet
WEL: Weight Efficacy Lifestyle
WOMAC: Western Ontario and McMaster Universities Osteoarthritis Index
WSSQ: Weight Self-Stigma Questionnaire
